## 11 Ethical Considerations

### 11.1 Good Clinical Practice (GCP)

The procedures set out in this Study Protocol are designed to ensure that M/s Arjuna Natural Extract Limited and Investigator abide by the principles of the Indian GCP, the basis of which lies in the Declaration of Helsinki; in the conduct, evaluation and documentation of this study. Ethics Committee notifications as per Good Clinical Practice Guidelines will also be followed during the conduct of the study.

### 11.2 Risk / benefit assessment

This study includes interventions offering the prospect of direct health-related benefit to the patient. To establish with certainty that the therapeutic efficacy of Amla Extract (AMX160) in Indian patients is not due to placebo effect; placebo comparator is selected. Patients enrolled in the study will have risk of lack of efficacy of study medication but all the patients will be encouraged for life style modification during the study period.

### 11.3 Ethics Committee review and communications

This Protocol, corresponding CRF, Informed Consent Documents (including Patient Information Sheet (PIS) and Informed Consent Form (ICF)) will be reviewed by the

|                                                                                  |                                                                                                       |                                                              |
|----------------------------------------------------------------------------------|-------------------------------------------------------------------------------------------------------|--------------------------------------------------------------|
| [figure not shown] | Clinical trial to evaluate efficacy and safety of Amla Extract (AMX160) in patients with Dyslipidemia | Project No. AN-03ASE
0115H2-SYN02
Ver.01, Dt: 01-01-15 |
|----------------------------------------------------------------------------------|-------------------------------------------------------------------------------------------------------|--------------------------------------------------------------|

registered Institutional Ethics Committee (IEC) / Institutional Review Board (IRB) of each study centre. The first subject must be enrolled only after the IEC/IRB approves the Protocol and other documents for the study. Ethics Committee notifications as per Good Clinical Practice Guidelines will be followed during the conduct of the study.

#### **11.4 Informed consent process**

Written informed consent from each of the patient will be taken prior his / her enrolment in the study and will be documented by the Investigator in the source document and will be preserved safely after the completion / termination of the study for at least a period of 5 years if it is not possible to maintain the same permanently. The Investigators and / or designated study personnel will explain the IRB / IEC approved Informed Consent Documents (including Patient Information Sheet (PIS) and Informed Consent Form (ICF)) and all relevant details of the study and the study medication to the patient (in English or in a language understandable to the patient) before initiation of the study regarding the purpose, procedures to be carried out, potential hazards, available alternative therapeutic modalities and rights of the patients. They will further be given a description of any foreseeable risks and discomforts. Patient will also be told that they have the right to opt out of the study at any time without having to give reasons if they so wish and without prejudice to further treatment. The patient will be given sufficient time to consider the implications of the study before deciding whether or not to participate in the study. The patient (or LAR in case of minor / mentally challenged) and the principal investigator must sign the informed consent form. A copy of the ICF signed by the investigator and patient and/ or LAR and/ or independent witness will be given to the patient. The patient should have legal capacity and be able to comprehend the nature, meaning, importance and risks of the study and to make up his mind accordingly. If the patient is unable to read and understand the necessary information pertaining to his participation in the study, then, an impartial witness (a person, who is independent of the trial and who cannot be influenced by people involved in the trial) would attend the informed consent process and would explain the contents of the informed consent form, in a language understood by the patient. Date must be mentioned along with the signature of each individual. No patient should be enrolled without obtaining his/ her written informed consent.

#### **11.5 Statement of subject confidentiality (including ownership of data and coding procedures)**

The data identifying each study subject by name will be kept confidential and will be accessible only to the Sponsor / Sponsor's authorized representative including QA auditors and / or CRA and if necessary to the IRB / IEC. The subjects will be identified throughout and after the completion of the study by allotted randomization numbers only (as mentioned in subject coding systems in "Test Product Management")

|                                                                                  |                                                                                                       |                                                              |
|----------------------------------------------------------------------------------|-------------------------------------------------------------------------------------------------------|--------------------------------------------------------------|
| [figure not shown] | Clinical trial to evaluate efficacy and safety of Amla Extract (AMX160) in patients with Dyslipidemia | Project No. AN-03ASE
0115H2-SYN02
Ver.01, Dt: 01-01-15 |
|----------------------------------------------------------------------------------|-------------------------------------------------------------------------------------------------------|--------------------------------------------------------------|

section of the Protocol). The subjects will be informed that their identity will not be revealed except to the above authorities.

#### **11.6 Financial considerations for the subjects**

The subjects will not have any financial burden for participating in the study. In the event of an injury occurring to the clinical trial subject, Sponsor will provide free medical management as long as required. In event of a trial related injury, sponsor will provide financial compensation to the subject for the injury. In case of trial related death, his/ her nominee would be entitled for financial compensation.

### **12 Study Monitoring and Supervision**

#### **12.1 Study monitoring**

Monitoring and auditing: Standard Operating Procedures developed by Clinical Research Organisation will be followed, in order to comply with Good Clinical Practice guidelines and to ensure acceptability of the study data for registration purposes. Checking of the Case Record Forms (CRFs) for completeness and clarity, and cross-checking with source documents in the presence of the Investigator giving due consideration of data protection and medical confidentiality will be required, and the investigator will assure M/s Arjuna Natural Extract Limited of necessary support at all times. This will be necessary to monitor the progress of the study. Monitoring will be done by the sponsor's designated person. Monitor would visit the study site at least once before, once during and once after the completion of clinical phase of trial at the study site.

#### **12.2 Study materials**

M/s Arjuna Natural Extract Limited would supply adequate study medications to the investigator through Clinical Research Organisation. Adequate study materials, including CRFs, study medication supplies will be provided to the Investigator by Clinical Research Organisation. All used and unused study medications and other unused study materials will be collected and must be returned to the sponsor after the clinical phase of the trial has been completed.

#### **12.3 Filling of Case Report Forms**

All entries in the Case Record Forms must be made legibly in ballpoint pen (not pencil, felt tip or fountain pen). All data collected during the study must be entered by the Investigator on the CRFs provided. A reasonable explanation must be given by the Investigator for the missing data, if any. The completed CRFs must be signed by the Investigator named in the study Protocol.

|                                                                                  |                                                                                                       |                                                              |
|----------------------------------------------------------------------------------|-------------------------------------------------------------------------------------------------------|--------------------------------------------------------------|
| [figure not shown] | Clinical trial to evaluate efficacy and safety of Amla Extract (AMX160) in patients with Dyslipidemia | Project No. AN-03ASE
0115H2-SYN02
Ver.01, Dt: 01-01-15 |
|----------------------------------------------------------------------------------|-------------------------------------------------------------------------------------------------------|--------------------------------------------------------------|

If the Investigator authorizes other persons to make entries in the CRF, the names, positions, signatures and initials of those persons must be provided to M/s Arjuna Natural Extract Limited. If a person other than the Investigator enters the findings in the CRF, that person must also sign the CRF.

If corrections are made to entries in the CRF by the Investigator or designate(s), the words or figures must be crossed through, leaving the initial entry legible. The correction must then be dated and initialled. Incorrect entries must not be covered with correcting fluid, obliterated, or made illegible in any way.

CRFs must be kept updated all the times. Arrangements will be made by the sponsor to collect the copy of CRFs on completion. Any missing or erroneous data entry in the CRF should be verified with the investigator and accordingly corrected by the investigator before data entry. Arrangements will be made by the sponsor to collect the copy of those CRFs.

#### **12.4 Data handling & record keeping**

All the subjects' findings including demographics will be recorded in source documents. Laboratory reports will also be considered as source documents. All the data captured in these source documents will be entered in the respective CRFs. All raw data and transcribed data forms will be compiled by the study personnel assisting in the study and will be checked, wherever applicable, for completeness. All data related to the study will be in the custody of the Investigator.

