After randomization, patients will be followed up on outpatient basis for period of 84 days (12 weeks) with scheduled visits on day 28, day 56 and day 84 post-randomization. Efficacy assessments will be carried out by laboratory investigations on each of the scheduled visits (except randomization visit). Clinical adverse events monitoring would be done on each visit and complete laboratory check-ups (both haematological and biochemical) and ECG will be repeated at the end of the study (12 weeks) so as to assess the safety of the study medication. Laboratory values obtained during the screening visit will be considered as baseline values for efficacy and safety analysis. Though every effort will be made to adhere to the schedule of visits, a window period of  $\pm 5$  days will be permitted for all the visits.

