#### **4.4 Brief discussion of study design**

This will be a randomized, double blind, parallel, placebo controlled, multicentre study to evaluate the efficacy and safety of Amla Extract (AMX160) 500 mg capsule of M/s Arjuna Extract Limited, Kerala compared to a placebo capsule in patients with dyslipidaemia. Randomization prevents selection / treatment allocation bias and blinding will prevent the bias in the assessment of efficacy and safety (adverse events) due to the study medication. Randomized patients will be simultaneously enrolled in either study group as per their randomization number and will be followed up in a parallel manner till the completion of study.

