#### The primary efficacy endpoint would be:

1. Mean percent change in TG levels at the end of 12 weeks in the two groups

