### **7.3 Laboratory Investigations**

A Central Clinical Pathology Laboratory will be used for all laboratory investigations. Methods to be used for the laboratory tests are specific to the Laboratory. Lab investigations to be conducted are; Haematological parameters include haemoglobin levels, total leucocyte count, Absolute Neutrophil Count (ANC), platelet count. Biochemical parameters include fasting blood sugar, blood urea, serum creatinine, serum bilirubin, SGOT, SGPT, TG, TC, LDL, HDL, VLDL, Apo A1, Apo B, hs-CRP, Homocysteine, HbA1C, TSH, CoQ10 and HMG Coenzyme Reductase activity. Serum pregnancy test will be done during screening and end of study in females of child bearing potential.

|                                                                                  |                                                                                                       |                                                              |
|----------------------------------------------------------------------------------|-------------------------------------------------------------------------------------------------------|--------------------------------------------------------------|
| [figure not shown] | Clinical trial to evaluate efficacy and safety of Amla Extract (AMX160) in patients with Dyslipidemia | Project No. AN-03ASE
0115H2-SYN02
Ver.01, Dt: 01-01-15 |
|----------------------------------------------------------------------------------|-------------------------------------------------------------------------------------------------------|--------------------------------------------------------------|

The schedule for laboratory test is shown in table below:

| Parameter                                                                                                     | Visit 1
Screening | Visit 2
(Day 0)* | Visit 3
(Week 4) | Visit 4
(Week 8) | Visit 5
(Week 12) |
|---------------------------------------------------------------------------------------------------------------|----------------------|---------------------|---------------------|---------------------|----------------------|
| Efficacy                                                                                               |                      |                     |                     |                     |                      |

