#### Visit 4: Follow-up visit (Day 56 $\pm$ 5)

- General physical and systemic examination
- Study Medication count
- Adverse event recording
- Concomitant diseases and medications
- Blood sample collection for laboratory analysis
- Dispensing Study Medication
- Instructions for lifestyle modification (healthy diet with aerobic exercise at least 4 days a week)

|                                                                                  |                                                                                                       |                                                              |
|----------------------------------------------------------------------------------|-------------------------------------------------------------------------------------------------------|--------------------------------------------------------------|
| [figure not shown] | Clinical trial to evaluate efficacy and safety of Amla Extract (AMX160) in patients with Dyslipidemia | Project No. AN-03ASE
0115H2-SYN02
Ver.01, Dt: 01-01-15 |
|----------------------------------------------------------------------------------|-------------------------------------------------------------------------------------------------------|--------------------------------------------------------------|

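### Week 4 and Week 8 lipid results pass through site source documents and CRFs with no masking, so site staff can see the primary-endpoint analyte during treatment and may be partly unblinded

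*Protocol*

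**What the plan says.** The primary endpoint is "Mean percent change in TG levels at the end of 12 weeks in the two groups". Section 4.3 states that "Efficacy assessments will be carried out by laboratory investigations on each of the scheduled visits (except randomization visit", and the table in section 7.3 schedules TG, LDL, HDL, VLDL, total cholesterol and FPG at Weeks 4, 8 and 12. Section 7.3 also says "A Central Clinical Pathology Laboratory will be used for all laboratory investigations".

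The data path is set in sections 12.3 and 12.4. Section 12.4 says "Laboratory reports will also be considered as source documents" and then "All the data captured in these source documents will be entered in the respective CRFs", and it places all study data in the investigator's custody. Section 12.3 says "All data collected during the study must be entered by the Investigator on the CRFs provided". It lets the investigator authorise others to make entries and requires CRFs to be kept up to date at all times.

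Blinding (sections 9.7 and 9.8) consists of matching capsules, centrally coded supplies and sealed envelopes or scratch cards. Neither section mentions laboratory results. Section 4.4 relies on this blinding: "blinding will prevent the bias in the assessment of efficacy and safety (adverse events) due to the study medication".

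Site staff have several points of contact with the patient after randomisation. Visits 3 and 4 both list "Instructions for lifestyle modification (healthy diet with aerobic exercise at least 4 days a week". Item 5 of section 6.3 allows withdrawal when the investigator or medical expert thinks continuing is not in the patient's best interest. Section 10.2.2 has the investigator judge adverse event severity and record the relationship to study medication.

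**The concern.** Matching capsules hide the treatment but not the response to it. If the treatment works, a TG result after randomisation carries information about the arm. A site that sees the Week 4 value can react to it, knowingly or not, by pressing diet and exercise harder, by judging that a patient is better off leaving, or by reading an adverse event differently. Certainty about the arm is not needed. Reacting to the result is enough, because results differ between arms when there is an effect.

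What is at stake is Week 12 TG, retention and the investigator-rated safety data. Retention matters most because section 14.4.3 makes the Per Protocol analysis definitive, the Per Protocol definition requires end-of-study laboratory values, and section 14.2 rules out imputation. A patient withdrawn after a poor lipid result therefore leaves the main analysis.

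**Working it through.** **Inputs.** Section 14.1 gives a between-group TG difference of 51, SD 76, allocation 1:1, two-sided alpha 5%, power 90%, 44 per group evaluable and 49 enrolled. Section 2 says most lipid-lowering agents reach peak action by 4 weeks, which makes some Week 4 signal plausible. The between-visit correlation is not in the protocol, so I assume 0.4 to 0.8.

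**The plan's own figure.** At the rounded effect size 0.7, a two-sample t-test needs 43.87, so 44 per group, and 44/0.9 = 48.9, so 49. The stated numbers reproduce. Nothing below changes them. I use the unrounded d = 51/76 = 0.671.

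**How much one TG result reveals.** For two normal groups of equal variance, d SDs apart and allocated 1:1, the best possible guess of arm is right with probability Φ(d/2).
- d = 0.671: Φ(0.336) = 0.631.
- d = 0.3 (assumption, smaller or slower effect): Φ(0.15) = 0.560.

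**How much two results reveal.** With the same d at both visits and correlation r, the combined separation is D = d × √(2/(1+r)).

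| r (assumed) | D | Φ(D/2) |
|---|---|---|
| 0.4 | 0.802 | 0.656 |
| 0.6 | 0.750 | 0.646 |
| 0.8 | 0.707 | 0.638 |

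These are ceilings. They assume a guesser who knows both distributions, uses the best cut-off, and sees the full planned effect already at Week 4.

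**Which routes the visit schedule leaves open.**
- *Visit 3 lifestyle instruction:* Week 4 blood is drawn at this visit, so on routine turnaround its result cannot shape the instruction.
- *Visit 4 lifestyle instruction:* the Week 4 result can be known by then. This is the one scheduled instruction that an on-treatment value can affect.
- *After Visit 4:* Visit 5 lists no lifestyle instruction. The Week 8 result can act only through withdrawal or unscheduled contact.
- *Adverse event severity and causality:* open from the time a result is seen.

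**Direction and size, as an illustration.** Suppose sites press hardest on the half of patients with the poorer Week 4 TG. At d = 0.671 that half holds Φ(0.336) = 63% of placebo and 37% of active patients, so extra effort goes mainly to placebo and narrows the gap.

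Now suppose the worst 10% overall on Week 4 TG are withdrawn, by one rule in both arms. On the SD scale, put the placebo mean at 0, the active mean at −0.671, and higher values as worse. The common cut-off is 1.018. It removes 1 − Φ(1.018) = 15.4% of placebo and 1 − Φ(1.018 + 0.671) = 4.6% of active patients. Of 49 per arm that is about 7.6 against 2.2 patients. The mean of those kept moves down by φ(c)/Φ(c) in each arm, where c is the cut-off's distance from that arm's mean. Carrying the difference in these shifts to Week 12 with correlation r, and a true difference of 51, gives a completer difference of 45.5 (r = 0.4), 42.8 (r = 0.6) or 40.0 (r = 0.8).

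**The case against.** The strongest reply is that this is a silence, not a stated release. No section says when the central laboratory returns Week 4 and Week 8 reports or to whom. Entries may be made by authorised persons other than the treating investigator, and section 12.4 has study personnel compile the data. That stands in part: receipt during treatment is a strong inference, not text. But the protocol does more than stay silent. It makes the reports source documents, puts the data in the investigator's custody and requires CRFs to be kept current, and an authorised person still works for the site.

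The second reply is that a central-laboratory TG assay is objective. Knowing the Week 4 value does not alter how Week 12 TG is measured, and section 4.4 speaks of bias in assessment. This stands for measurement of the primary endpoint. It does not cover behaviour, retention or investigator-rated safety.

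The third reply is that the routes are narrow. The lifestyle instruction is worded alike for everyone, no withdrawal criterion names a lipid value, lipid-affecting medication is already barred (sections 6.3 and 9.6), and tolerability is graded by fixed adverse event criteria. All of this stands. It limits the concern to the open routes listed above without closing them.

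Two stronger readings are tempting. A reader might infer that the results reveal allocation. The protocol's own planning figures do not support that, since about a third of best guesses would still be wrong. A reader might also infer that selective withdrawal inflates the effect. Under one rule applied in both arms it shrinks it. Inflation would need a different rule, which nothing in the protocol suggests.

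**Conclusion.** The point holds in a limited form. As written, the protocol lets site staff see the primary-endpoint analyte during treatment, and its blinding provisions do not address this. The consequence is partial unblinding and room for response-driven behaviour. The 63% and 64-66% ceilings rest on the planning effect being real and already present when the blood is drawn. The 64-66% figure also rests on the assumed correlation, and it does not apply to scheduled lifestyle advice, which only the Week 4 result can reach.

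The likeliest distortions would work against finding a difference. The 40-46 range for completers depends on the invented 10% withdrawal rule and shows only that the definitive analysis does not absorb such a pattern. Neither the primary assay nor the sample size is called into question. The change should be made because the gap is avoidable and the trial's credibility rests on its double blind.

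**What to change.** In sections 7.3, 12.3 and 12.4:

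- State that post-randomisation lipid results are not released to sites, patients or monitors before database lock. Screening lipids still go to the site, since eligibility depends on them.
- Have the central laboratory transfer these results directly to the trial database, and remove the fields from the site CRF.
- Keep safety results reported to sites. CBC, liver, renal and TSH tests are not scheduled at Weeks 4 and 8, so the open case there is FPG. State whether it is handled as an efficacy or a safety result at those visits.
- Define a central-laboratory alert route so that a medically important value still reaches the investigator, and record each use of it.

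The cost is protocol and laboratory-manual wording plus setting up the transfer and the alert route with a laboratory already in use. Visits, blood draws and sample size do not change.
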